#### Control arm

Participants randomized to the control arm will receive an email informing them of their assignment to the control arm. We reviewed the treatment as usual practices we believe to be related to the outcomes of interest in this trial and found that all sites have at least one social worker or financial advocate that is able to help patients access routinely available financial assistance programs in the hospital and wider community, including American Cancer Society support for transportation to and from appointments and temporary lodging as needed for treatment. Participants in the treatment and control arms will be provided with information on financial toxicity and contact information for their social worker or financial advocate. They can make use of any and all financial, material, and psychosocial support programs they encounter in the course of the trial. Participants are free to engage in other clinical trials during the course of this trial.

#### Modifications

Participants in the intervention arm may discontinue UCT payments at any time. Although we have taken every step to protect public benefits eligibility during the course of the trial there may be some interactions that we are not yet aware of, and each participant can work with the GI manager to weigh the costs and benefits of participation relative to currently unforeseen public benefits interactions. If a participant in the intervention arm dies during the 12-month intervention period, their debit card will be transferred to their designated beneficiary which is required to be next of kin or a caregiver. Having a caregiver or next of kin, however, is not required to participate in the study. In that case payments will not be redirected. If participants change cancer clinics or receive additional cancer care from another clinic, they will be able to remain in the trial. See Figure 2 for the GIFT Trial participant flow diagram.

**Figure 2 F2:**
[figure not shown]
Participant flow diagram provides an overview of the study flow from recruitment through data collection. RA, Research assistant; GI, Guaranteed income.

### Outcomes

#### Primary outcome measures

The primary outcomes of interest are financial toxicity, quality of life, and treatment adherence. Primary outcomes will be measured at baseline, 3, 6, 9, and 12 months.

##### Financial toxicity

Financial toxicity will be measured using the Comprehensive Score for Financial Toxicity (COST), a validated, 11-item patient-reported outcome measure of cancer-related financial hardship that captures three domains of financial hardship (also described as *financial toxicity*): resources, affect, and financial. Scores range from 0 to 44 and lower scores indicate greater financial hardship. COST scores have been associated with quality of life, anxiety and depression (de Souza et al., 2014, 2017).

##### Health-related quality of life

Quality of life will be measured using the Rand 36–Item Short Form Health Survey (SF-36) (RAND Corp, 2022). The SF-36 is scored to produce eight subscales: physical functioning, role limitations due to physical health, role limitations due to emotional problems, energy/fatigue, emotional wellbeing, social functioning, pain, and general health. Each subscale has a score ranging from 0 to 100, produced by coding and averaging the survey responses.

##### Treatment adherence

Treatment adherence questions were developed by Gany et al. Costas-Muniz et al. (2016) to identify barriers to cancer treatment among low-income and immigrant cancer patients. The first question asks if the respondent has missed any of the following appointments in the last three months: chemotherapy/infusion, radiation, general oncology, follow-up, or any other cancer-related appointment. If the respondents indicates yes, they are asked to identify a reason for missing each of the identified appointments: did not have childcare, could not afford transportation to appointment, could not afford copayment, could not afford insurance deductible, was not covered by insurance, prior approval was not obtained, I forgot about my appointment, I was scared/anxious, or other, please describe: (free text). The second question asks if the respondent has missed a dose of cancer-related medication in the last three months and if so, select a reason why: forgot to take it, forgot to buy/pick it up, not covered by insurance, no insurance, could not afford copayment, no time to buy/pick up, do not think they will work/help, do not like the side effects, could not afford transportation to the pharmacy, other, please describe (free text). The outcome variable is binary (yes/no to having missed any appointment or medication dose in the past 12 months).

#### Secondary outcome measures

The secondary outcomes of interest are anxiety and depression, food insecurity, housing stability, and general economic indicators. Secondary outcomes will be measured at baseline, 3, 6, 9, and 12 months.

##### Anxiety and depression

Anxiety and depression will be measured with the Hospital Anxiety and Depression Scale (HADS), a 14-item scale that is considered the gold standard for measuring anxiety and depression in cancer patients. Scores range from 0 to 21 on each subscale (anxiety and depression) and higher scores indicate greater likelihood of anxiety or depression (Zigmond and Snaith, 1983; Vodermaier and Millman, 2011; The Hospital Anxiety Depression Scale, 2021).

##### Food insecurity

To measure food insecurity we will use the USDA 6-item Short Form Food Security Survey (United States Department of Agriculture, 2021).

##### Housing stability

We derived a 7-Item tool from the American Housing Survey to assess housing instability (Bureau, 2023).

##### Economic and employment variables

We will collect data on weekly hours of employment, interruptions in employment and work reductions, income sources, employment protections, essential expenses (housing, transportation, utilities, food), general impact of cancer on finances, estimated amount of personal savings and estimated amount of total credit card debt.

#### Exploratory outcome

Mortality is long-term exploratory outcome that will be measured at 2, 3, and 5 years from baseline.

##### Mortality

The intervention's potential impact on mortality will be explored using the Social Security records of all participants in the study. Mortality data from the Social Security records will be reviewed at 2, 3, and 5 years post-enrollment. The proportion of deceased participants from the intervention and control groups will be determined and compared. See Table 1 for GIFT Trial outcomes, data sources and measurement timepoints.

**Table 1 T1:** GIFT Trial measures.

**Outcome (measure)**	**Data source**	**Baseline (T1)**	**3m (T2)**	**6m (T3)**	**9m (T4)**	**12m (T5)**	**2–5 years**
Demographic	Survey	X					
Employment, income, savings, debts, public benefits utilization		X	X	X	X	X	
Cancer type/stage		X					
Treatment nonadherence		X	X	X	X	X	
Financial toxicity (COST)		X	X	X	X	X	
Quality of life (FACT-G)		X	X	X	X	X	
Anxiety and Depression (HADS)		X	X	X	X	X	
Food insecurity (USDA)		X	X	X	X	X	
Housing instability (AHS)		X	X	X	X	X	
Mortality	Social security records						X

### Sample size

The sample size was determined by the amount of philanthropic funding we secured for the Trial which was sufficient to provide $12,000/year to 100 participants. After accounting for anticipated attrition we determined that a 250 person sample was needed – 100 in the intervention group and 150 in the control group (overrecruited for differential attrition). We conducted power analyses based on the literature and pilot study findings to determine detectable treatment effects in the primary outcomes of interest. Power analyses methods and results for each primary outcome are described below. Recruitments sites were selected for serving racially diverse, low-income patient populations. Our pilot study sample was 50% Black, 35% white, 4% Asian, 4% mixed, and 7% other. 52% of the sample identified as Hispanic or Latino.

### Recruitment

Each week the study team will use the electronic health record to view upcoming clinic appointments (in the next 2–3 weeks) and determine the study eligibility of the patients with upcoming appointments. A research assistant (RA) will contact each eligible patient's physician/nurse practitioner/physician assistant to let them know that the patient has been selected for recruitment to the study and the RA would like to meet with them prior to or after the upcoming appointment. The RA will also contact scheduling department to let them know that the patient is eligible for the study and will be approached at the upcoming appointment—both the receptionist and provider will be asked to tell the patient about the study and prepare them to be approached by the RA. The RAs will keep a participant tracking sheet and will record each step of approach and engagement. On the day of the appointment, the RA will approach the patient and use a designated quiet space to complete the informed consent (on paper) and Qualtrics baseline survey (on their phone, the RA's tablet, or with the assistance of the RA reading questions to them). The RA will provide the participant with information on financial toxicity and the contact information for their social worker or financial advocate at this time.

### Allocation

Each week participants with completed baseline surveys in Qualtrics will be randomly assigned to one of the study conditions using a computer generated 1:1.5 randomization schedule stratified by age and recruitment site. We will over recruit for the control arm to compensate for an expected 30% differential attrition rate (an estimate derived from yet unpublished U.S. guaranteed income RCTs). Randomization schedule will be stored in a password protected excel spreadsheet that can only be accessed by the principal investigator and senior research coordinator who are not involved in the day-to-day recruitment of participants.

### Data collection methods

All primary and secondary outcomes are patient-reported and will be collected using an online survey administered at baseline, 3, 6, 9, and 12 months post-enrollment. At baseline, the participants will also answer questions about their age, gender, race, education, cancer type, cancer stage, new or recurrent cancer diagnosis, household income, public benefits utilization, employment status and hours worked per week. At each data collection time point, participants will receive an email or text message with a survey link and directions for completing it. A RA will also call the participant to ask if they would like to complete the survey with them over the phone. Greenphire Clincards will be mailed to the participant's address at the 3-month data collection point and filled with $30 for each survey they complete. For the exploratory outcome of mortality, we have partnered with Social Security Administration who will provide aggregate data on participant mortality, earnings, and disability benefits at 2, 3, and 5 years from study enrollment.

#### Retention

A $30 incentive will be provided for each survey completed. Starting at each data collection time point, the study team will continue to contact the participant by email, text, and phone twice per week for 6 weeks until the survey is completed. We will call next of kin/caregiver if the survey is not completed within three weeks. If the survey is not completed within eight weeks of the data collection time point, the survey items will be treated as missing data. If response rate drops to 75% in any arm, the incentive will be increased to $50 per survey for participants in that arm of the trial.

#### Data management

Completed consent forms will be stored in a private institutional server maintained by the PIs University. Survey data will be entered and stored in Qualtrics, an online data collection and storage platform. The Qualtrics platform provides a high level of data safety and security that is HIPAA compliant for the collection and storage of personally identifiable information (Qualtrics, 2023). During periods of data analysis, data will be exported from Qualtrics to Stata SE17 as a .data file. The data will be stored in and accessed using Box, a secure cloud based platform that conforms to global compliance requirements for data privacy (Box, 2023). To protect confidentiality, we will only collect information from the participants that is essential to the study's aim of understanding the impact of UCTs on cancer patients' health and treatment outcomes. Participant's names, dates of birth, and treatment status will be collected from the electronic medical record for the purposes of outreach prior to the study. The research team will keep this information in a single, password protected excel spreadsheet stored on and accessible through a secure online document sharing platform. This information will be used to contact potential participants over the phone or at their next clinic appointment. We will maintain the contact information of all potential participants even if they decline to participate or are found ineligible in order to conduct feasibility analyses. Participants who enroll will provide identifiable personal information that will be linked to the survey data until data collection and analysis are complete. When the study is complete the data will be de-identified and stored in a secure online database with unique identifiers. The unique identifiers will be linked to the participant's personal information (name, date of birth, contact information) on a single, password protected excel spreadsheet stored on the principal investigator's password protected personal computer. Social Security Numbers (SSN) will be collected at study enrollment and entered directly into a separate, high security server maintained by the PI's University. To protect participants' eligibility for public benefits, each month the PI or Senior Research Coordinator will transfer participant SSNs and trial group allocation directly to SSA through its secure Government to Government Services Online application.

### Statistical methods

All survey data will be entered into and stored in Qualtrics, then analyzed using StataSE 17 or later, SAS v. 9.4 or later, and/or R v. 4.2.2 or later. The following descriptive statistics will be reported side-by-side for the treatment and control group at baseline: age (mean/SD and % over 64); gender (% per category); race (% per category); cancer type and stage (% per category); new or recurrent cancer diagnosis (% per category); baseline food security (mean/SD); baseline housing stability (% experience homelessness); income (mean/SD in U.S. dollars per year); employment (mean/SD in hours per week); ECOG score (% per category), COST score (mean/SD), treatment nonadherence in last 90 days (% yes). To determine if randomization was balanced Chi-square (or, if necessary due to sample size restrictions, Fisher's Exact Tests) will be used for categorical variables and independent *t*-tests (or, if non-normal, Kruskil-Wallis Tests) will be used at baseline, and between drop-outs and completers in each condition.

Linear mixed models will be used for all primary and secondary continuous outcomes over time. We will assess differences between treatment and control group after controlling for possible confounding variables. General estimating equations (GEE) with a logit link and binary distribution will be used for all binary primary and secondary outcomes over time. We will assess the odds ratio between treatment and control groups after controlling for possible confounding variables. GEEs with a log link and poisson distribution will be used for all non-binary, categorical primary and secondary outcomes over time. We will assess the risk ratio between treatment and control groups after controlling for possibly confounding variables.

Linear mixed-models and GEEs were selected because of the longitudinal nature of the study in which repeated measures will be collected across five timepoints. This approach will allow us to integrate observations from all five data collection time points into the statistical models. We plan to adjust these models by accounting for age, gender, race, new or recurrent cancer diagnosis, baseline food security, baseline housing stability, and baseline ECOG. These likely covariates were selected because they represent factors that have been associated with financial toxicity, quality of life and nonadherence in past studies (Altice et al., 2016; Yabroff et al., 2018). We suspect these variables will be correlated with the outcome variables, however, correlation structure will be determined at time of analysis.

Mortality as a long-term exploratory outcome will be analyzed at each time point separately. Chi-square (or, if necessary due to sample size restrictions, Fisher's Exact Tests) will be used to test for differences between the treatment and control groups. Logistic regressions will be used at each time point and will control for age, gender, race, new or recurrent cancer diagnosis, baseline food security, baseline housing stability, and baseline ECOG.

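### For a multi-level categorical outcome, the planned log-link Poisson GEE estimates a ratio of mean category codes, not the risk ratio the article promises

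*Protocol article*

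**What the plan says.** The Statistical methods section of the protocol article sets out three model classes by type of outcome.

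- Continuous outcomes go to linear mixed models.
- Binary outcomes go to a logit model: "General estimating equations (GEE) with a logit link and binary distribution will be used for all binary primary and secondary outcomes over time". The effect measure is an odds ratio.
- The remaining class has its own rule: "GEEs with a log link and poisson distribution will be used for all non-binary, categorical primary and secondary outcomes over time". The effect measure follows at once: "We will assess the risk ratio between treatment and control groups after controlling for possibly confounding variables".

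No coding, reference level, dichotomy or level-by-level indicator is attached to the third rule, and no outcome is named as belonging to it.

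Under Secondary outcome measures, general economic indicators are listed as secondary outcomes measured at all five time points. The section on economic and employment variables then includes "interruptions in employment and work reductions, income sources, employment protections", together with numeric items such as weekly hours, savings and credit card debt. Food insecurity is to be measured with the "USDA 6-item Short Form Food Security Survey" and housing with a 7-item derived tool. Neither section gives the scoring.

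**The concern.** A log-link Poisson model yields a risk ratio when the outcome is 0/1, and a mean or rate ratio when it is a count. The article applies it to neither: the class is defined as non-binary and categorical. There the model treats the numeric labels of the levels as quantities and compares their averages. For ordered levels the answer changes with the numbering. For unordered levels, such as types of income source, no numbering is right.

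At stake is the reporting of some secondary results. A figure labelled as a risk ratio would not be one, and a reader would misjudge both its size and what it refers to. Because the coding is not fixed, it could also be chosen after the data are seen.

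**Working it through.** The article gives no figure for this analysis, so there is none to reproduce. The check has two parts: which outcomes the rule can reach, and what the model estimates.

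**1. Which outcomes are in the class**

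- COST is a score: "Scores range from 0 to 44 and lower scores indicate greater financial hardship". Not in the class.
- SF-36 is a set of scores: "Each subscale has a score ranging from 0 to 100". Not in the class.
- Treatment adherence is defined as yes/no. It goes to the logit GEE.
- HADS is a 0 to 21 score on each subscale. Not in the class.
- Food security and housing: scoring is not stated. The baseline table is to show food security as a mean with SD and housing as a percentage experiencing homelessness. These are baseline summaries and do not fix the outcome scale, but they point away from multi-level categories.
- Economic and employment items: several are numeric. Income sources, employment protections, and work interruptions or reductions could be categorical. Their response formats are not stated.

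**2. What the model estimates**

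The model is log E(Y) = a + b × arm (+ covariates), so exp(b) = E(Y | intervention) / E(Y | control). If Y is 0/1, E(Y) is a probability and exp(b) is a risk ratio. If Y holds codes c1, c2, c3 with probabilities p1, p2, p3, then E(Y) = Σ c·p and exp(b) is a ratio of mean codes.

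Illustration with **assumed** probabilities (not from the article): control 0.40/0.30/0.30, intervention 0.50/0.30/0.20.

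| Codes | Intervention mean | Control mean | Ratio |
|---|---|---|---|
| 1-2-3 | 0.5+0.6+0.6 = 1.7 | 0.4+0.6+0.9 = 1.9 | 0.895 |
| 0-1-2 | 0+0.3+0.4 = 0.7 | 0+0.3+0.6 = 0.9 | 0.778 |
| 0-1-3 | 0+0.3+0.6 = 0.9 | 0+0.3+0.9 = 1.2 | 0.750 |
| 2-1-0 | 1.0+0.3+0 = 1.3 | 0.8+0.3+0 = 1.1 | 1.182 |
| 1-0-2 | 0.5+0+0.4 = 0.9 | 0.4+0+0.6 = 1.0 | 0.900 |
| 2-3-1 | 1.0+0.9+0.2 = 2.1 | 0.8+0.9+0.3 = 2.0 | 1.050 |

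The actual risk ratios in the same data are 0.50/0.40 = 1.25, 0.30/0.30 = 1.00 and 0.20/0.30 = 0.667 for the three levels, and 0.50/0.60 = 0.833 for the middle level or above. No row of the table equals any of them. Adding 1 to every code moves the estimate from 0.778 to 0.895. Reversing the order does not even give the reciprocal: 1/0.778 = 1.286, against 1.182. The last two rows show that, for unordered levels, an arbitrary choice of labels can change the direction.

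A Poisson GEE with exchangeable correlation was fitted to simulated data with these probabilities (8,000 and 12,000 subjects, four visits, latent correlation 0.6). It gave 0.896 (1-2-3), 0.779 (0-1-2), 1.178 (2-1-0) and 0.897 (1-0-2), in line with the algebra. Fitted to one 0/1 indicator per level, the same model gave 1.241, 1.008 and 0.662, close to the true level-specific risk ratios.

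**The case against.** The strongest reply concerns reach. The article does not show that any outcome is a multi-level category. The primary outcomes and HADS are scores or binary, the baseline summaries suggest a numeric food security score and a yes/no housing item, and much of the economic list is numeric. If the remaining items are asked as yes/no questions, the logit GEE already covers them. This stands as a limit on severity. It does not rescue the sentence, which fixes a model and an effect measure that do not match for the class it names.

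A second reply is that the authors may intend one 0/1 indicator per level, for which the risk ratio would be correct, and that such coding is often left to an analysis plan. But the text labels the class non-binary and sends binary outcomes to a logit link, so this reading goes against the stated rule. If instead an outcome is a true item count, its mean ratio is interpretable, but it is still not a risk ratio.

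A reader might infer more than the article supports in three ways.

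- The sentence mentions primary outcomes, but no primary outcome is multi-level, so the primary analyses are untouched.
- The economic indicators are listed as secondary outcomes, but neither the research hypothesis nor the secondary objectives name them, so the study's main claims do not rest on this rule.
- One might also conclude that the standard errors will be wrong. In the control arm of the illustration the variance is 0.69 under either coding, so a model-based Poisson error would be too large by √(1.9/0.69) = 1.66 with codes 1-2-3, or √(0.9/0.69) = 1.14 with codes 0-1-2. Both errors are conservative, both vanish with the robust variance usual in GEE, and the article does not specify model-based errors. The wrong effect measure remains under either variance.

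**Conclusion.** The concern holds as a mismatch between model and effect measure. As written, the rule would report a ratio of mean codes as a risk ratio for any outcome analysed as a multi-level category. That the estimate depends on the coding follows from the form of the model and does not rest on the assumed probabilities; the particular values (0.750 to 1.182 in the table for the same data) do.

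The reach is narrow: secondary outcomes only, most plausibly some economic and employment items, and food security or housing only if they are categorised. Whether those items are multi-level cannot be settled from the article. Severity is low to moderate.

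**What to change.** Replace the sentence on non-binary categorical outcomes in Statistical methods, and name the outcomes it covers with their coding.

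- **Ordered levels:** a cumulative-logit GEE or mixed model, reported as an odds ratio.
- **Nominal items:** pre-specified 0/1 indicators, analysed either with the logit GEE already planned (odds ratio) or with a log-link Poisson GEE and robust variance (risk ratio). The second option needs a stated exception to the rule that all binary outcomes use the logit link.
- **True counts:** keep the log-link Poisson GEE with robust variance, and call the estimate a mean or rate ratio.

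If no outcome turns out to be in the class, delete the sentence.

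The cost is one paragraph of text, with no change to data collection or sample size. The small downside is that the effect measure is renamed for some secondary outcomes, and a nominal item split into indicators gives several estimates instead of one.

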#### Trial design

The GIFT Trial is designed as a randomized, controlled, unblinded, multicenter superiority trial with two parallel groups and a combined primary endpoint of financial toxicity, quality of life, and treatment adherence. Randomization will be performed as block randomization with a 1:1.5 allocation stratified by age and treatment center.

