#### Power analysis for primary outcomes

All power calculations were conducted in Power Analysis and Sample Size (PASS) 2023. Power was calculated at alpha=0.05 with 200 patients at five timepoints. For all power estimates, we assumed an 8% mortality rate between primary timepoints; therefore, 28% of patients will be deceased by the 12 month time point (American Cancer Society, 2019). Power calculations were conducted with missing timepoints rather than on imputed data since we plan to compare imputed to non-imputed models. We further assumed an exchangeable correlation structure with a moderately strong intraclass correlation (r = 0.6).

Many estimates were obtained through the pilot analysis. We conducted an observational, pre-test/post-test pilot study in which we recruited 150 financially burdened cancer patients and provided them with a one-time grant of $1,000. We measured primary and secondary outcomes of interest prior to the intervention delivery and two months after to examine changes over time. We expect that the full trial, which will provide participants with 12 times the amount of cash that was provided in pilot, will yield higher treatment effects. We believe the estimates from the pilot are conservative estimates for the full trial, and any estimates not obtained from the pilot were overly conservative to ensure full power.

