#### Missing data

Patterns of missing data (due to mortality and otherwise) will be analyzed. If the missing appears relatively random, multiple imputation will be used; otherwise, missingness will be addressed through last observation carried forward (LOCF). Imputed results will be compared to non-imputed results. A secondary analysis for all primary and secondary outcomes will be to test for dependence (through interactions) between treatment and time.

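### Read as written, the primary models put the pre-randomisation visit under a single treatment term without baseline-outcome adjustment, which would shrink the estimated effect by about 20 to 28% and cost COST power

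*Protocol article*

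**What the plan says.** Under Primary outcome measures: "Primary outcomes will be measured at baseline, 3, 6, 9, and 12 months". Under Allocation, the baseline survey comes before assignment: "Each week participants with completed baseline surveys in Qualtrics will be randomly assigned to one of the study conditions".

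Statistical methods assigns linear mixed models to continuous outcomes and GEEs to binary and categorical ones. It describes the target as a difference, odds ratio or risk ratio between the arms, and says of the modelling: "This approach will allow us to integrate observations from all five data collection time points into the statistical models". The plan is to "adjust these models by accounting for age, gender, race, new or recurrent cancer diagnosis, baseline food security, baseline housing stability, and baseline ECOG". Baseline COST, SF-36, HADS and nonadherence are not on that list, nor is recruitment site, although Trial design specifies "block randomization with a 1:1.5 allocation stratified by age and treatment center".

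The interaction appears only under Missing data: "A secondary analysis for all primary and secondary outcomes will be to test for dependence (through interactions) between treatment and time". The power section matches the five-visit description: "Power was calculated at alpha=0.05 with 200 patients at five timepoints".

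**The concern.** Together these statements leave baseline COST, SF-36 and nonadherence a place only as outcome rows, with one treatment term covering all visits. That term averages a visit where no effect is possible with four visits where one is. Its expected value is smaller than the effect during the payment period, and a larger sample does not correct that.

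COST is the only primary outcome that the article presents as well powered; SF-36 is stated at 0.1831 to 0.3294 and nonadherence at 0.065 to 0.095. Any attenuation therefore falls on the one outcome best able to show a benefit. The plan also leaves out a strong predictor that it already collects, each patient's own starting score.

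Two smaller matters belong here. Food insecurity and housing stability are secondary outcomes measured from baseline, and their baseline values are also listed covariates, so in those models the baseline value could stand on both sides. And center is a randomisation stratum that no model includes.

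**Working it through.** **Inputs.** From the power section: alpha 0.05 (taken as two-sided), 200 patients (taken as 100 per arm), five visits, 8% loss per interval, exchangeable correlation ρ = 0.6. From its COST and SF-36 paragraphs: differences 2.4 and 3.4, SDs 7.1 and 29.4, covariate correlation R from 0.5 to 0.8. Assumed here: no effect at baseline, the full effect constant from month 3 to month 12, and the same monotone loss in both arms.

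**1. The stated power.** Retention by visit is 1, 0.92, 0.846, 0.779, 0.716, with mean 0.852. With the full difference at all five visits,

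SE = SD × √(1 − R²) × √[((1 + 4ρ)/5) × (2/100) / 0.852], where (1 + 2.4)/5 = 0.68 and the last root is 0.1263.

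- COST, R = 0.5: SE = 7.1 × 0.866 × 0.1263 = 0.777; z = 2.4/0.777 = 3.09; power Φ(3.09 − 1.96) = 0.871 (stated 0.867).
- COST, R = 0.8: SE = 7.1 × 0.6 × 0.1263 = 0.538; z = 4.46; power 0.994 (stated 0.993).
- SF-36 by the same formula: 0.183 and 0.332 (stated 0.1831 and 0.3294).

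**2. Weight of the baseline visit.** With complete data it is 1/5, so the term recovers 0.80 of the effect. With loss, the shares of patients whose last visit is m = 1 to 5 are 0.080, 0.0736, 0.0677, 0.0623 and 0.7164. Under GLS:

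- Information per patient: Σ p_m × m/(1 + (m − 1)ρ) = 0.080 + 0.092 + 0.0923 + 0.0890 + 1.0535 = 1.4068.
- Part from baseline: Σ p_m/(1 + (m − 1)ρ) = 0.080 + 0.046 + 0.0308 + 0.0222 + 0.2107 = 0.3897.
- Baseline share: 0.3897/1.4068 = 0.277, so the term recovers 0.723.

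With independence weights the share is 1/(5 × 0.852) = 0.235. A true COST effect of 2.4 is thus estimated on average as 2.4 × 0.80 = 1.92 down to 2.4 × 0.723 = 1.74. For ρ from 0.3 to 0.8 the GLS share runs only from 25.8% to 28.8%.

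**3. Power of the single five-visit term, by GLS throughout.** SE in SD units is √(0.02/1.4068) = 0.1192 at 100:100 and √[(1/100 + 1/150)/1.4068] = 0.1088 at 100:150.

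| COST | SE | z = 1.735/SE | Power | Stated |
|---|---|---|---|---|
| 100:100, R = 0.5 | 0.733 | 2.37 | 0.658 | 0.867 |
| 100:100, R = 0.8 | 0.508 | 3.42 | 0.927 | 0.993 |
| 100:150, R = 0.5 | 0.669 | 2.59 | 0.737 | 0.867 |
| 100:150, R = 0.8 | 0.464 | 3.74 | 0.963 | 0.993 |

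A simulation of the 100:100, R = 0.5 case (4,000 runs) gave 28.5% attenuation and power 0.646. SF-36 power at 100:100 becomes 0.125 to 0.214.

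**4. Four post-baseline visits, no baseline adjustment.** With k = m − 1, information is Σ p_m × k/(1 + (k − 1)ρ) = 1.2666 and SE is √(0.02/1.2666) = 0.1257 SD. COST z is 3.11 and 4.48, and power is 0.874 to 0.994.

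**5. Arms constrained equal at baseline.** Information is Σ p_m × k/[(1 − ρ)(1 + kρ)] = 2.543 and SE is √(0.02/2.543) = 0.0887 SD. With no other covariates, z = 2.4/(7.1 × 0.0887) = 3.81 and power is 0.968. The single five-visit term without covariates has z = 1.735/(7.1 × 0.1192) = 2.05 and power 0.536. The standard error falls by 1 − 0.0887/0.1192 = 26%, and the estimate is not attenuated.

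**The case against.** The strongest reply is that the single-term model is inferred. The article writes no equation, visit coding or contrast. It calls its covariates likely ones and defers the correlation structure to the analysis. Using all five time points is compatible with a constrained-baseline model, which would remove the attenuation, and a condensed article may leave such detail to an analysis plan that is not shown. This stands to the extent that every figure in step 3 is conditional on the reading. It does not dispose of the point, because the elements that create the reading are stated, not omitted: five visits in the models, a covariate list without the outcome's baseline value, and the interaction made secondary. Nothing in the article contradicts the reading.

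Three stronger inferences are tempting, and the document does not support them.

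- A reader might infer that the power calculation assumed a treatment effect at baseline. Step 1 comes close to the stated range on that assumption, but step 4 gives 0.874 to 0.994 without it. Under the same GLS, the full effect at all five visits gives 0.906 to 0.997, a worse match. The stated power cannot settle which model was used.
- A reader might put COST power as low as 0.60. That figure pairs the GLS attenuation with the standard error from the averaged-retention formula in step 1. A consistent GLS calculation gives 0.658 at that end, and the planned 100:150 enrolment gives 0.737.
- A reader might conclude that the primary test is invalid. It is not. With no effect at any visit, the averaged term is also zero.

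**Conclusion.** The concern holds as a conditional one. On the natural reading of the article, the primary treatment coefficient recovers about 0.72 to 0.80 of the post-baseline effect. COST power is about 0.66 to 0.93 with 200 patients at 1:1, or 0.74 to 0.96 with 100:150, below the stated 0.867 to 0.993 at each end. The consequence is attenuation and lost power, not false positives.

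These figures assume a full, constant effect from month 3 and equal loss in the arms. The higher control-arm attrition that the article expects under Allocation is not modelled and could lower the 100:150 figures. The practical loss is for COST, since SF-36 power is already stated as low; nonadherence was not recomputed. Omitting center is a separate, minor mismatch with the stratification. It does not cause the attenuation, and its effect on power cannot be computed from the document.

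**What to change.** - State that the primary contrast is the treatment difference averaged over months 3, 6, 9 and 12, with treatment-by-visit terms in the model.
- For continuous outcomes, either use those four visits as responses with the baseline value of the same outcome as covariate, or keep baseline as a response in a mixed model with the arms constrained equal there. In the GEEs, do the analogous thing: post-baseline visits as responses and the baseline value of the outcome as covariate.
- For food insecurity and housing stability, use the baseline value in one role only.
- Separately, add treatment center to every model and keep age.
- Restate power for this contrast. On the plan's inputs with 100 per arm, COST power is about 0.97 with the baseline constraint and no other covariates.

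The cost is analysis wording and a rerun of the power calculation; every variable needed is already collected.
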